## Abstract

**Background:**

Mindfulness has shown positive effects on mental health, mental capacity and well-being among adult population. Among children and adolescents, previous research on the effectiveness of mindfulness interventions on health and well-being has shown promising results, but studies with methodologically sound designs have been called for. Few intervention studies in this population have compared the effectiveness of mindfulness programs to alternative intervention programs with adequate sample sizes.

**Methods/design:**

Our primary aim is to explore the effectiveness of a school-based mindfulness intervention program compared to a standard relaxation program among a non-clinical children and adolescent sample, and a non-treatment control group in school context. In this study, we systematically examine the effects of mindfulness intervention on mental well-being (primary outcomes being resilience; existence/absence of depressive symptoms; experienced psychological strengths and difficulties), cognitive functions, psychophysiological responses, academic achievements, and motivational determinants of practicing mindfulness.

The design is a cluster randomized controlled trial with three arms (mindfulness intervention group, active control group, non-treatment group) and the sample includes 59 Finnish schools and approx. 3 000 students aged 12–15 years.

Intervention consists of nine mindfulness based lessons, 45 mins per week, for 9 weeks, the dose being identical in active control group receiving standard relaxation program called Relax. The programs are delivered by 14 educated facilitators.

Students, their teachers and parents will fill-in the research questionnaires before and after the intervention, and they will all be followed up 6 months after baseline. Additionally, students will be followed 12 months after baseline. For longer follow-up, consent to linking the data to the main health registers has been asked from students and their parents.

**Discussion:**

The present study examines systematically the effectiveness of a school-based mindfulness program compared to a standard relaxation program, and a non-treatment control group. A strength of the current study lies in its methodologically rigorous, randomized controlled study design, which allows novel evidence on the effectiveness of mindfulness over and above a standard relaxation program.

**Trial registration:**

ISRCTN18642659. Retrospectively registered 13 October 2015.

## Background

In the contemporary society, children and adolescents have to deal with several stressors on daily basis. Stressors may arise from family-system disturbances, peer conflicts, school context, socio-cultural challenges, vulnerabilities to physical and mental health problems, or from living in the fast-paced, media-saturated and multi-tasking world that sets high demands for performance, success and competition [1]. Research suggests that sustained stress in childhood and adolescence has negative influence on mental health, general functioning, and specific learning-related factors, such as executive function and working memory [2]. Approximately one fourth of youth suffers from at least one mental disorder during the past year, and respectively, about one third suffers from any lifetime mental disorder. Anxiety disorders are the most frequent mental disorders in children and adolescents, followed by behavior disorders, the mood disorders and substance use disorders [3]. In Finland, approximately 14 % of children aged eight to nine years suffer from some kind of mental health problems, and this share steeply arises along with the onset of puberty to 15–25 % in adolescent population [4]. Psychiatric disorders are the most important disorder group that impairs adolescents’ functional ability [5], and perceived stress is shown to increase the risk of subsequent mental disorders and their symptoms [6–8]. Thus, there is a need for effective, disseminable strategies to protect children and youth from dysfunctional effects of stress.

During the last few years, research on mindfulness has increased, and extended from initially focusing only on adults to including children and adolescents as well. However, studies with methodologically sound designs are still lacking. To be able to indicate the significant beneficial effects of mindfulness practice also on children’s and adolescents’ health and well-being, research needs to shift toward large, well-designed studies with robust methodologies, and adopt standardized formats of interventions, allowing for replication and comparison of studies, to develop a firm evidence base [9].

## Mindfulness and health

Mindfulness refers to a non-condemning state of awareness and readiness to pay attention to the stream of experiences in the present moment [10]. The concept is rooted in Eastern contemplative traditions and was later developed as part of therapeutic applications in psychology and medicine, such as mindfulness-based stress reduction (MBSR) [10, 11], mindfulness-based cognitive therapy [12], dialectic behavior therapy [13], and acceptance and commitment therapy (ACT) [14, 15]. The beneficial elements of mindfulness are suggested to include e.g. attention regulation, body awareness, emotion regulation, and change in perspectives on the self and learning [16]. Research among adults has shown that mindfulness practices reduce negative states of mind, such as stress [17], and symptoms of anxiety and depression [18–20], as well as alleviate various medical conditions, such as chronic pain [10] , type 2 diabetes [21, 22] and attention-deficit hyperactivity disorder [23, 24].

Furthermore, research among adults has shown promising positive associations between mindfulness practice and health behaviours, such as smoking cessation [25, 26], decreased binge eating [27], and decreased alcohol and substance use [28]. Finally, practicing mindfulness has also been shown to produce positive effects on psychological well-being in healthy participants [29–31].

Recently, also brain imaging has been utilized to study the neural level effects related to mindfulness based practices or meditation. Changes are reported both in structural properties [32, 33] and in brain functioning [19, 34], especially related to attentional control [35] and emotion regulation [36, 37].

In the previous decade, interest started to spread to mindfulness based approaches with children and adolescents and international research has shown promising preliminary results both in clinical context [23, 38–42] and in non-clinical, school context [43–49].

## Mindfulness among children and adolescents in school setting

It has been reported that mindfulness interventions are acceptable for children and adolescents, as well as feasible, and that they improve for example attention, emotional reactivity and some areas of meta-cognition [1]. Mindfulness-based programs have improved school-aged children’s attention and teacher-rated social skills [45]. A school-based (RCT) study showed significant improvements in post-treatment measures of self-rated test anxiety, teacher rated attention, social skills, objective measures of selective (visual) attention but no sustained attention, as well as improved behavioral regulation, metacognition, and overall global executive control among children who started out with poor executive functions [43]. Correspondingly, in another study [44] adolescents with lower pre-intervention self-regulation were observed to experience greatest improvements in behavioral regulation, meta-cognition and executive function. Preliminary research has shown that school-based mindfulness intervention programs may also result in beneficial outcomes regarding the interaction and pedagogical atmosphere among both students and students and their teachers [50].

In the school setting, mindfulness interventions reach the whole age group, and through the equal reach may even act as a counterforce for the prominent development of increasing inequality between different groups (based on e.g. gender, learning difficulties, health challenges, or socioeconomic background), yet empirical evidence is lacking.

While cost-effectiveness and ease of implementation of mindfulness programs in schools are notable advantages, sufficient evidence is still lacking on the role of mindfulness in fostering resilience, mental health and well-being among children and adolescents, over and above existing approaches such as relaxation. The previous studies conducted among youth are still few in number [1, 9, 23, 38–40, 43–45, 51, 52], and their methodological shortcomings (e.g. small sample sizes without control groups and/or unstandardized mindfulness intervention programs) prevent making generalizations of the efficacy of these interventions [9]. For instance, it is not well understood whether the observed changes persist or what the short and long-term effects of mindfulness intervention are [40]. Further, the role of mindfulness in improving health behavior among adolescents is not well known [53, 54].

It might be at place to state here also that the Finnish school system offers exceptionally good possibilities for examining between-individual variation as the school-related variance is minimized due to the homogenous schools system of our country: All schools follow the national curriculum, private schools are almost non-existent, and majority of students go to the nearest school in their residential area. Also areal segregation is still rather low compared to other countries. Furthermore, all teachers receive university education which reduces the teacher-related variance.

## The aim of the study

The comprehensive aim of this ongoing trial is to examine the effects of mindfulness practices in strengthening children’s and adolescents’ internal resources that promote mental wellbeing, cognitive functions, psycho-physiological responses, academic achievement, health behavior, motivational determinants of practice compared to a standard relaxation program and a non-treatment group (waiting-list). The primary aim is to determine the effectiveness of the school-based mindfulness program on three main outcomes: resilience (RS14), existence or absence of depressive symptoms (RBDI), and experienced psychological strengths and difficulties (SDQ). Secondary outcomes include mindfulness, happiness, satisfaction with life, quality of life, positive and negative affects, compassion/self-kindness, the rumination, and stress. Other explored factors among children and adolescents are cognitive functions, psycho-physiological responses, academic achievement, health behavior, motivational determinants of practicing mindfulness, and class room social environment. The study will also explore equity of distribution of the primary outcomes in terms of social background, gender, and learning difficulties of the students. The results of the study will be presented according to the 2010 CONSORT statement [55] and its extension to cluster randomized controlled trials [56].

## Methods

### Trial design

The study is an ongoing cluster randomized controlled trial (RCT) with three arms. Eligible schools were randomly allocated either to an intervention, control or non-treatment groups. Clusters were school classes (grades 6, 7 and 8) and age gap was from 12 to 15 years olds. The data collection started in the spring 2014, and finishes in the autumn 2016. The analyzing and reporting of the data starts in the autumn 2016.

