### Randomization procedure

The recruitment started by listing all the schools in a Southern part of Finland. After choosing the schools (including as many classes of the same grade as possible), a letter explaining the study procedure was sent by e-mail to the head masters. Within few days after sending the information letter, the research team members called the headmasters by telephone. In most schools the decision to take part to the study was made collectively by the head master and the class teachers (of the chosen grades). The schools were enrolled from 14 cities/municipalities during the collection of the data (years 2014–2016). Altogether 247 schools were contacted, 59 of those participated in the study participation percentage being 24. In each municipality we aimed at an equal number of intervention and control classes. In order to achieve balanced intervention and control groups, schools participating in the study were randomized using the available background variables. The selection of intervention-control pairs was primarily based on the language being used for teaching (Finnish, Swedish or English, the grade, the school location, the number of classes participating in the investigation and, if necessary, the average apartment price per square meter in the school’s neighborhood).

The classes were randomly assigned to mindfulness intervention classes (*N* = 85) and control classes (*N* = 79) and non-treatment classes (*N* = 28). Due to practical reasons, in spring 2014 and in autumn 2015 schools were divided into two arms (intervention and control) and in spring 2015 and spring 2016 into three arms instead of two: intervention, control and non-treatment groups. First, the schools were divided into three groups based on the school location and the average apartment price per square meter. Within each of these groups, the total number of schools and classes varied. Next, the schools for these groups were divided into three subgroups including approximately same number of classes (some schools were combined into one subgroup to achieve an as even distribution of classes as possible).

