## Sample size

The sample size was estimated to detect the mean difference of 0.2 standard deviation units (effect size = 0.2) on main outcomes of risk for depression (RBDI), social/emotional/behavioural skills (SDQ) and resilience (RS14) between intervention and control groups with 80 % power and the two-tailed 5 % level of significance. The clustering of outcomes within schools was taken into account, assuming an intra-cluster (intra-school) correlation coefficient of 0.03 and assumed that on average 60 children in each school will complete the study. The required sample size was estimated to be 1090 children per group, and allowing for about 10 % drop-out rate, the study requires 1200 children per group and total of 2400 children to be recruited. On the RBDI and SDQ total difficulties score, an effect size of 0.2 corresponds to a mean decrease of 0.8 score on the RBDI scale and a mean decrease of 1.0 score on the SDQ scale, assuming the standard deviations of 4 for RBDI [62] and 5 for SDQ [61]. The effect size of 0.2 corresponds to a mean increase around 2.5 score on the resilience scale, assuming the standard deviation of 13 [70].

In addition to comparing the intervention and control groups, we were interested in comparing the intervention and non-treatment groups in order to gain even more strength into the study design. However, this was not our primary intrest. Since the previous research has shown also standard relaxation programs to have beneficial effects on well-being, we are expecting to find greater differences between intervention and non-treatment groups compared to intervention and control groups. Using the same assumptions to detect the mean difference of 0.3 standard deviation units (effect size of 0.3) between intervention and non-treatment group, the required sample size was estimated to be 486 children per group, and allowing for about 10 % drop-out rate, the study requires 540 children in the non-treatment group.

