## Analysis plan

Data will be analyzed on an intention to treat basis including all randomized classes in the groups to which they were randomly assigned. Descriptive statistics (mean, median or percentages as appropriate) will be used to summarize the baseline characteristics and outcomes in each group.

Statistical analysis will be done with multilevel (hierarcial) models to account for the clustering within schools. Continuous outcomes will be analysed with linear mixed effects models and categorical outcomes with generalized linear mixed effects models. Maximum likelihood estimation will be used to get unbiased and efficient parameter estimates for data with missing values in the follow-up measurements.

The effectiveness of the mindfulness intervention on primary and secondary outcomes will be first analyzed using unadjusted analyses and then adjusted for age, sex and baseline values of the outcomes. The modifying effect of factors (i.e. sex, childen’s age, health status, circumstances at home, social relationships, hobbies, school achievement) on the effectiveness of mindfulness will be analysed using tests of interactions. Interaction analyses are exploratory in nature. The differences in the continuous outcomes between groups will be presented using mean differences with 95 % confidence intervals. Results are expressed using odd ratios with 95 % confidence intervals for categorical outcomes. Two-sided statistical tests with a 5 % level of significance will be used.

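### The randomised unit is given as both school and class, while the sample size and the model name school clustering only; if classes of one school could be in different arms, treatment-effect standard errors would be too small whenever class-level variance exists.

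*Protocol article*

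**What the plan says.** The protocol article gives two answers on the unit of allocation.

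- **School.** Trial design: "Eligible schools were randomly allocated either to an intervention, control or non-treatment groups". Randomization procedure: "schools participating in the study were randomized using the available background variables". The same section describes dividing schools among arms term by term and merging some schools to even out the number of classes.
- **Class.** Trial design, in the sentence after the one on schools: "Clusters were school classes". Randomization procedure: "The classes were randomly assigned to mindfulness intervention classes", with 85 mindfulness, 79 relaxation and 28 non-treatment classes. The intention-to-treat definition in Analysis plan also treats classes as the randomised units.

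The statistical sections name the school only. Sample size: "The clustering of outcomes within schools was taken into account", with an intra-school correlation of 0.03 and 60 completers per school. Analysis plan: "multilevel (hierarcial) models to account for the clustering within schools". No class-level term or class-level correlation appears anywhere.

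**The concern.** In a cluster trial the treatment effect must be judged against the variation between the units that were allocated. The protocol leaves open which units those are, and its model commits to one of the two candidates.

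Correlation within a class is plausible here. Both programmes are taught as group sessions by a small set of facilitators, and the trial itself measures the classroom social environment. If classes in the same school could go to different arms, a model with a school intercept alone would treat pupils in a class as independent given their school. The confidence intervals and p-values for all three primary outcomes would then be too optimistic.

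If schools were the unit, the inference is sound but the description is not. A reader would count 192 randomised clusters where there are at most 59. The article undertakes to report under the CONSORT extension for cluster trials, so the unit has to be unambiguous.

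**Working it through.** **1. Which unit does the sample size use?** For 0.2 SD, 80% power and two-sided 5%:

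- Unclustered n per group = 2 × (1.960 + 0.842)² / 0.2² ≈ 393.
- Design effect = 1 + (60 − 1) × 0.03 = 2.77.
- 393 × 2.77 ≈ 1089, against 1090 stated.
- For 0.3 SD: 175 × 2.77 ≈ 485, against 486 stated.

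The stated figures reproduce, so the calculation takes the school as the cluster.

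**2. Cluster dimensions.**

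- Classes (Randomization procedure): 85 + 79 + 28 = 192.
- Pupils (baseline counts in Data collection timeline): 523 + 1090 + 821 + 203 + 254 + 109 = 3000.
- Pupils per class: 3000/192 = 15.6. Classes per school: 192/59 = 3.3.

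The check uses a balanced layout near these values: 50 schools, k = 4 classes per school, m = 16 pupils per class. The school correlation is the document's 0.03. The class correlation ρ is **assumed** over a range. Total variance is set to 1, so the residual is e = 1 − 0.03 − ρ.

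**3. Classes allocated within schools (two per arm), school intercept only.**

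- True variance of the treatment effect is proportional to e + mρ.
- The model uses the pooled within-school mean square instead: MS = [(k − 1)(e + mρ) + k(m − 1)e] / (km − 1).
- Ratio of model SE to true SE: r = √[MS / (e + mρ)].
- True type I error = 2 × [1 − Φ(1.96 r)].

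Example, ρ = 0.02: e = 0.95; e + mρ = 1.27; MS = (3 × 1.27 + 60 × 0.95)/63 = 0.965; r = √(0.965/1.27) = 0.87; type I error = 8.8%.

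| Assumed class ICC | SE ratio, formula | Type I error, formula | Type I error, simulation (3000 runs) |
|---|---|---|---|
| 0 | 1.00 | 5.0% | 5.8% |
| 0.01 | 0.93 | 6.8% | 7.3% |
| 0.02 | 0.87 | 8.8% | 8.1% |
| 0.05 | 0.75 | 14.4% | 14.6% |

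**4. Whole schools allocated, same model.** The variance of a school mean is 0.03 + ρ/k + e/(km). The between-school variation estimates all of it, including the class share. In simulation over the same four values the SE ratio was 0.99 to 1.01 and the type I error 4.8% to 5.8%.

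**5. Contrasts within a class.** For treatment by sex, with both sexes in each class, the SE ratio was 0.99 to 1.04 under either unit.

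**6. Does class allocation make the trial too small?** If school effects cancel within schools, n per group = 393 × (1 + 14.6 × ρ). This gives about 451 at ρ = 0.01 and 681 at ρ = 0.05, both below 1090.

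**The case against.** The strongest reply is that the text points away from the harmful case. Schools are said to be divided among arms, some schools are merged into one subgroup, and most matching variables describe the school (its location, its number of participating classes, local apartment prices). Balance of classes was sought within municipalities, not within schools. Nowhere is a school said to be split between arms. The sentence with 85, 79 and 28 can be read as counting classes that followed their school. On that reading the school-only model gives close to nominal error. An article may also leave the full random-effects structure to the analysis plan, and a multilevel model does not exclude a class level.

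Much of this stands, and it makes whole-school allocation the likelier reading. It does not remove the contradiction. Three statements still make the class the cluster or the randomised unit, and the only level the model names is the other one.

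A reader might infer more than the document supports:

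- *That every standard error is too small.* Within-class contrasts are not understated (step 5). The treatment effect is affected only if schools were split and class variance exists beyond school.
- *That the planned sample is too small.* It is not, even under class allocation (step 6).
- *That naming maximum likelihood commits the plan to normal-based tests.* Analysis plan mentions it in connection with missing follow-up data and names no test distribution.

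**Conclusion.** The contradiction over the randomised unit is certain; its statistical effect is conditional. If classes of one school could be in different arms, the school-only model understates treatment-effect standard errors by about 7%, 13% or 25% for class correlations of 0.01, 0.02 or 0.05. The type I error is then about 7%, 9% or 14%. With no class variance beyond school it stays at about 5%. These figures rest on assumed class correlations and on every school being split evenly between arms.

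If whole schools were allocated, which the described procedure suggests, the planned model is adequate for the treatment effect. The error then lies in the statements that classes were the clusters and were randomised, since the randomised units number at most 59. The point is a low-cost clarification and safeguard. It does not show that the primary analysis is invalid.

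**What to change.** 1. State one unit of allocation, and say whether classes of the same school could ever be in different arms.
2. Correct the sentences that conflict with it in Trial design, Randomization procedure and the intention-to-treat definition in Analysis plan. If the unit is the school, give the number of schools per arm beside the class counts.
3. Specify random intercepts for school and for class within school in the primary models.

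The cost is corrected wording and one more variance term. Under school allocation the extra term leaves the treatment inference essentially unchanged; under class allocation it protects it. It requires each pupil's class to be on the analysis file. The document does not state this, but its class counts by arm make it likely. By the article's own timeline, data collection was still running and analysis had not begun, so the change can precede any results.
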